### 2.2. Procedure

The participants who are referred to the mental health unit for having fulfilled the requirements to be candidates for BS, will be evaluated to see if they meet the rest of the inclusion criteria for this study. In Table 1, it can be seen the selection criteria used to choose the appropriate candidates to receive the BS. These criteria are based on the European Guidelines for Obesity Management in Adults, which indicates that a comprehensive obesity management can only be accomplished by a multidisciplinary obesity management team [44].

Participants’ evaluation and selection will be carried out by the clinical psychologists and psychiatrists of the mental health unit of the Regional Hospital of Vinaròs (Castellón). The clinical psychologists who will participate in this trial will be in charge of collecting all the information from the participants (alphanumeric codes assigned to the participants will be entered to safeguard their anonymity). The coded information will be given to the author [name] to introduce it in the database and then, returned to the center.

Participants who have received the approval for BS by the multidisciplinary health team and also have met the inclusion criteria by the clinician (see “Eligibility criteria” section), will be invited to participate in the study through an informative document. They will also be provided with confidentiality and informed consent documents. After accepting to participate, an email will be sent to participants with a link through which they will be able to complete the pre-treatment evaluation on the Qualtrics survey platform [45]. Then, they will be informed by phone of the experimental condition to which they will have been randomly assigned, which may be 8, 12, or 15 days baseline assessment, and they will then complete online the baseline assessment protocol on the same platform [45]. Randomization to the different baselines will be done with randomizer software (www.randomizer.org). Randomization will be performed by a researcher unrelated to the study using the computer-generated sequence mentioned. In the program, the researcher will generate one set of 60 numbers, which will have a one to three range. Participants will be randomly assigned to the 8, 12 or 15 baseline days.

The baseline and psychological intervention will be conducted between the period of acceptance for BS and the BS implementation, that last approximately one year in public health settings. The intervention will be carried out in an online group format through the Cisco Webex platform. The UP will be applied in twelve weekly 2-h online group sessions. To comply with the experimental design of the multiple baseline, when each participant completes the baseline evaluation, they will receive the first online session in individual format (to receive the first session in stages), then they will continue with the second session and the rest of the treatment in group format. The content of each session is shown in Table 2. Participants will receive the therapy support manual [11]. The online group will consist of five to eight participants, one therapist ([name]), and one co-therapist ([name]). For ethical reasons, if any of the patients feel uncomfortable during the study with the online group format, they may leave the group and receive individual onsite attention (treatment as usual). In this case, the content and estimated number of sessions will be the same, although the frequency will be stipulated by the mental health unit depending on its possibilities.

The study plans to conduct a follow-up assessment every three months until two years after treatment completion. All follow-ups will be conducted online. Considering the time interval of the baseline, the psychological intervention and the BS procedure, the two first follow-ups (three and six months after intervention) will be conducted before BS, and the rest will be conducted after BS. In addition, at the baseline and during treatment, the participants must fill out an online survey made up of 14 questions that will ask about the intensity of the emotions of happiness, sadness, anxiety, other emotions, difficulties in emotion regulation, body image, and emotional eating. Through this weekly evaluation, we expect to observe how the participants evolve in the different variables throughout the different treatment modules.

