A random assignment will be carried out to reduce the threat of selection, and the fact of choosing three conditions is one of the established standards for this type of designs in order to reduce the threat of ambiguous temporal precedence and maturation [38]. Furthermore, the fact that all three conditions involve evaluation periods of 8, 12 and 15 days is due to the established standard of having a minimum of five data points in each phase to reduce the threat of attrition [38]. By choosing at least eight, we make sure to meet it even considering the probability that participants will forget to fill out the assessment one day. Actually, the reason for choosing those days is the temporal stability of the variables that we measured through the study.

In addition, the intervention will begin in a staggered manner with individual sessions (to reduce the threat of the history) and to reduce the threat of testing, a pre-treatment assessment will be performed prior to starting the baseline, to consider that the assessment process itself can have therapeutic effects on participants [38].

The study includes five assessment moments (pre-treatment, baseline, treatment, post-treatment, and follow-up, one every three months until two years after treatment completion). The flow chart of the study design is shown in Figure 1.

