### 2.1. Sample and Recruitment

The study recruitment will start in September 2020 until December 2024. The study will be conducted in a public mental health center in Spain (Mental Health Unit of the Regional Hospital of Vinaròs, Castellón). Participants will be people over 18 years of age who have anxious or depressive symptoms, or at least one diagnosis of EDs according to Diagnostic and Statistical Manual of Mental Disorders five edition criteria [39] and who have been selected for a subsequent BS.

To calculate the sample size, we drew on a study that proposed stepwise rules of thumb for pilot studies based on the target effect size and the size of the future trial [40]. Previous works that study the efficacy of CBT procedures either in person or online have shown large variations in effect sizes, obtaining mainly medium to large effect sizes [41,42]. Taking these data into account, and expecting a 90% powered main trial and assuming a sample loss of 35% [43] we established a sample size of 20 participants per experimental condition for the present study, that is, a total sample of 60 participants.

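### The random list described in section 2.2 is simple randomisation and does not deliver the 20 participants per baseline condition stated in section 2.1

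*Protocol article*

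**What the plan says.** Section 2.1 (Sample and Recruitment) fixes the size: "we established a sample size of 20 participants per experimental condition for the present study", and then "that is, a total sample of 60 participants". It also assumes a loss of 35%.

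Section 2.2 (Procedure) describes how the sequence is made. A researcher unrelated to the study uses randomizer software to "generate one set of 60 numbers, which will have a one to three range". It continues: "Participants will be randomly assigned to the 8, 12 or 15 baseline days". No block, quota or stratum is mentioned.

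Section 2 (Materials and Methods) explains the role of the three conditions: "choosing three conditions is one of the established standards for this type of designs". It ties them to the threats of ambiguous temporal precedence and maturation, and ties the staggered individual start to the threat of history. Section 2.2 puts this into practice with an individual first session once each participant's own baseline ends. After that, treatment is in groups: "The online group will consist of five to eight participants". The article does not say how participants are placed in groups.

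**The concern.** The article states the allocation step positively: one set, 60 values, range one to three. Sixty values from three possibilities must repeat, and nothing holds the number of each value at 20. Taken as written, each participant's condition is an independent draw, so the condition sizes vary by chance around 20. The number in section 2.1 and the method in section 2.2 do not match.

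What is at stake is the replication of the effect at three different start points. The study has no untreated control, and section 2 rests experimental control on introducing treatment at staggered times. A condition well below 20 provides fewer replications at that baseline length, and the assumed 35% loss reduces them further. A second, weaker worry concerns the therapy groups. Under simple randomisation a group of five to eight may contain only two of the three lengths, so it has two start points instead of three.

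**Working it through.** **Inputs.** Total 60 and 20 per condition (section 2.1); one set of 60 numbers in the range 1 to 3 (section 2.2); therapy groups of 5 to 8 (section 2.2). Two assumptions are added. Each condition has probability 1/3, as the range implies. For the group-level figures only, groups are filled in enrolment order without regard to baseline length.

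**The plan's own figure.** 3 × 20 = 60, so the total agrees with the size per condition. The 20 itself cannot be rebuilt, because the article does not give the number before attrition that its rule of thumb produced.

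**Step 1: chance of the stated split.** The three counts are multinomial (60; 1/3, 1/3, 1/3).

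P(20/20/20) = 60! / (20!³ × 3⁶⁰) = 0.0136, that is 1.4%, or about 1 list in 73.

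**Step 2: how far the counts stray.** One condition's count is binomial (60, 1/3). Its mean is 20 and its SD is √(60 × 1/3 × 2/3) = √13.33 = 3.65. The 2.5% and 97.5% points are 13 and 27. Summing the exact multinomial over all splits gives:

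| Event | Probability |
|---|---|
| All three conditions within 18 to 22 | 22.9% |
| Smallest condition 16 or fewer | 49.0% |
| Smallest condition 15 or fewer | 31.7% |
| Smallest condition 14 or fewer | 18.8% |
| Largest minus smallest 8 or more | 47.0% |

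The expected smallest condition is 16.3 and the expected largest is 23.8. All these counts are at assignment, before dropout.

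**Step 3: groups lacking a length (conditional on the fill-order assumption).** For n independently assigned members,

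P(at least one length absent) = 3(2/3)ⁿ − 3(1/3)ⁿ.

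For n = 5 this is (96 − 3)/243 = 93/243 = 38.3%. For n = 8 it is (768 − 3)/6561 = 765/6561 = 11.7%.

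**Step 4: what each remedy does to the groups.** For a shuffled list holding exactly 20 of each number, P(absent) = [3·C(40,n) − 3·C(20,n)] / C(60,n). With permuted blocks of 3, any five consecutive places include one whole block wherever the run starts, so the probability is zero.

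| Group size | Simple list | Shuffled 20/20/20 list | Permuted blocks of 3 |
|---|---|---|---|
| 5 | 38.3% | 35.3% | 0% |
| 6 | 25.9% | 22.8% | 0% |
| 7 | 17.4% | 14.4% | 0% |
| 8 | 11.7% | 9.0% | 0% |

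A fixed 20/20/20 list therefore repairs the totals but hardly changes the groups. Blocks of 3 repair both.

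**The case against.** The strongest reply is that imbalance does little harm here. Missing 20 by one or two is of no consequence, so the 1.4% taken alone overstates the problem. The analyses in section 2.6 are pooled repeated-measures tests over time, individual reliable change indices and visual analysis of slopes. None of them compares 8, 12 and 15 days. Section 2.6 also expects fewer than 50 participants, in line with 60 × 0.65 = 39 after the assumed loss, so 20 per condition is a recruitment figure and not an analysed one. Even an expected smallest condition of about 16 leaves many single-case replications. All of this stands, and it limits the weight of the point.

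A reader might go further and infer three things that the article does not support.

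- **That power is lost.** No planned test uses condition sizes, so there is no analysis whose power would fall.
- **That every therapy group must contain all three lengths because its members are one another's concurrent controls.** Section 2 says that each participant can be their own control. Its three-condition standard applies to the study as a whole, and 60 participants in three conditions meet it. A group with two lengths is still staggered. All members sharing one length is rare: 3(1/3)ⁿ is 1.2% for groups of five and 0.05% for groups of eight.
- **That 12% to 38% of groups will lack a length.** This follows only if groups are formed without regard to baseline length. Deliberate composition could lower it.

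What the reply does not remove is the mismatch itself. Section 2.1 states 20 per condition, and the procedure written in section 2.2 does not secure it.

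**Conclusion.** The point holds at the level of the list. As described, allocation is simple randomisation. It gives the stated 20 per condition in 1.4% of lists and leaves some condition with 16 or fewer in about half of them. This rests on equal allocation probabilities and on reading section 2.2 as it stands, with no unstated quota.

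The group-level consequence is secondary and conditional: 38% of groups of five down to 12% of groups of eight would lack a length at assignment if groups are filled in enrolment order. It would mean a weaker stagger within those groups, not a breach of a written rule. The issue is modest in size, but it is worth correcting because the remedy is nearly free.

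**What to change.** In section 2.2, replace the single set of 60 numbers with one continuous sequence of permuted blocks of 3, that is, 20 sets each containing the numbers 1, 2 and 3 once in random order. The same outside researcher should generate and hold it, and the block size should be hidden from the recruiting clinicians. This gives exactly 20/20/20 when 60 are enrolled. It also places all three lengths in any five or more consecutive enrolees, before dropout.

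A continuous sequence is preferable to restarting blocks within each therapy group. Restarting needs group membership to be known at randomisation, whereas the article describes consecutive recruitment and individual assignment.

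The cost is a different list and one amended sentence. Sample size, visits and treatment do not change. The downside is that, if the block size becomes known, some assignments can be predicted. This matters less than in a trial comparing treatments, because every participant is planned to receive the same intervention.

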The specific objectives pursued are: to evaluate adherence to treatment and clinical improvement in the primary and secondary measures after applying the UP and to study its long term clinical usefulness until two years after the intervention. Thus, the main hypotheses proposed for this study are: (1) statistically significant differences (reliable change index; RCI) will be obtained between the scores obtained at the pre-treatment, baseline, and post-treatment on the primary and secondary measures; (2) the improvements obtained after the application of the UP will be maintained in the long term (follow-ups of up to two years); (3) participants in the pilot study will report high adherence rates and high satisfaction scores regarding the treatment delivery format and its components.

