The multiple baseline design involves the application of the treatment variable in a staggered way over time, through different observational units. This design is suitable for health services research interventions that are focused on changing patient behavior. This methodology facilitates a systematic comparison of pre-intervention and post-intervention measures [35], and conducting a preliminary assessment of a novel intervention [36]. Like randomized controlled trials (RCTs), the multiple baseline design can demonstrate that a significant change in behaviour has occurred and that is result of the intervention. One of the main limitations is that each participant must show changes only when the intervention is applied, and this issue, at a practical level is complicated, can make it difficult for the researcher to draw clear conclusions about the impact of the intervention. In order to reduce this limitation and improve the internal validity, researchers start treatment at different times across settings, behaviors, or people [37]. The multiple baseline design has advantages over the RCTs because this design requires fewer population groups and communities and they may act as their own controls [35]. In this sense, researchers often use this design with several people at once addressing the issue of external validity [37].

In the present investigation, all consecutive patients who are selected to undergo BS and who present anxiety or depressive symptoms or at least one diagnosis of ED, will be asked to participate. Once inclusion criteria are met (see “Inclusion and exclusion criteria” section), each patient will be randomly assigned to one of the multiple baseline conditions: 8, 12, or 15 evaluation days before the intervention. These multiple baseline conditions have been chosen following the current guides for single-case designs [34,38].

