#### 2.5.1. Primary Outcomes

Primary and secondary diagnosis according to the DSM-5 criteria will be evaluated with the International Neuropsychiatric Interview (MINI [50]). Subclinical symptoms of anxiety and depression will be evaluated through the Beck Depression Inventory-II (BDI-II [46,47]) and the Beck Anxiety Inventory (BAI [48,49]). The weight gain or loss of the participants will be evaluated through the Body Mass Index (BMI).

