To prove this, longitudinal studies are needed and some limitations regarding the interventions (specific CBT versus transdiagnostic intervention) and the delivery formats (onsite versus online) must be considered. The use of the UP in an online group intervention format in a public mental health setting with people waiting for BS has the following benefits:It can allow clinicians to use a single treatment for those candidates who present different EDs, with comorbidity, and also with subclinical symptoms or unspecified disorders [15].In other public health systems similar to the Spanish one, where onsite specific CBT is the most common delivery format, and therapy sessions occur at long intervals (e.g., more than a month) due to waiting lists, a UP online group intervention can help to increase the frequency of sessions and reduce costs because there are more patients treated simultaneously (five to eight patients in the same group), which can facilitate better patient care.Thanks to the online format, this intervention will facilitate access to psychological interventions in those candidates who face mobility challenges due to their obesity condition [31]. This innovative approach would be in line with the goals of the World Health Organization proposed in the mental health action plan to use electronic technologies to expand the delivery of mental health care [83].The fact of receiving quarterly follow-ups up to two years after treatment allows guaranteeing the prevention of relapses and maintaining the results, especially beyond the year and a half or two years, which is the moment in which the literature recognizes that pre-BS problems tend to reappear [42].Furthermore, this advantage offered by long term relapse prevention follow-ups leads to a condition of reduced healthcare costs that are associated with the care of comorbid health problems in this type of patients [3].And finally, it is known that group therapy provides benefits to the patient that are not obtained with individual treatment, such as reducing isolation, facilitating social support, and learning from the experiences of others [33], which could improve its efficiency.

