**Contraindications**
Relative
- Clearly unfavorable family environment
- Personality disorder
- Psychogenic vomiting
- Hyperphagia in other psychological disorders or other eating disorders
- Mild intellectual disability
- Psychotic disorders without positive symptoms
- Any psychiatric illness that significantly hinders the good follow-up and completion of the guidelines and medical indications for this process and may worsen the patient’s state of health
Absolute
- Drug dependency
- Moderate or severe intellectual disability
- Psychotic disorder with positive symptoms
- Bulimia nervosa

**Table 2 ijerph-17-06155-t002:** Treatment content split by session.

Session Number	Content
Session 1	Setting Goals and Maintaining Motivation
Session 2	Understanding your Emotions: What is an Emotion?
Session 3	Understanding your Emotions: Following the ARC (Antecedent, Response, Consequence)
Session 4	Mindful Emotion Awareness—I
Session 5	Mindful Emotion Awareness—II
Session 6	Cognitive Flexibility—I
Session 7	Cognitive Flexibility—II
Session 8	Countering Emotional Behaviors
Session 9	Understanding and Confronting Physical Sensations
Session 10	Putting it into Practice: Emotion Exposures—I
Session 11	Putting it into Practice: Emotion Exposures—II
Session 12	Recognizing Accomplishments and Looking to the Future

**Table 3 ijerph-17-06155-t003:** Distribution of the variables administered throughout the intervention.

Measures	Pre-Treatment	Baseline	Treatment	Post-Treatment	Follow-Ups ^1^
Demographic characteristics	X				
MINI	X			X	X
BDI-II	X			X	X
BAI	X			X	X
BMI	X	X	X	X	X
PANAS	X			X	X
NEO-FFI	X			X	X
QLI	X			X	X
EuroQol	X			X	X
MI	X			X	X
DERS	X			X	X
BEAQ	X			X	X
PHLMS	X			X	X
ERQ	X			X	X
Surgical Complications	X				
BITE	X			X	X
BSQ	X			X	X
EES	X			X	X
OASIS			X		
ODSIS			X		
OESIS			X		
PESIS			X		
STQ				X	X
Baseline assessment battery ^2^		X			
Assessment battery during treatment ^3^			X		

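### Six of the eight follow-ups fall after bariatric surgery, so maintenance from 9 to 24 months cannot be credited to the Unified Protocol, and follow-up stops short of two years after surgery

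*Protocol article*

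**What the plan says.** - **Timetable.** Section 2.2 places the baseline and therapy in the interval between acceptance for surgery and the operation, "that last approximately one year in public health settings". Follow-ups are quarterly for two years from the end of treatment, and "the two first follow-ups (three and six months after intervention) will be conducted before BS, and the rest will be conducted after BS".
- **Hypothesis 2** (section 1): "the improvements obtained after the application of the UP will be maintained in the long term (follow-ups of up to two years"). Table 4, under individual results, repeats this for the primary and secondary measures, using the Reliable Change Index (RCI) between pre-treatment or post-treatment and the follow-ups.
- **Primary outcomes** (section 2.5.1) are the MINI diagnosis, BDI-II, BAI and BMI: "The weight gain or loss of the participants will be evaluated through the Body Mass Index (BMI"). Table 3 schedules all four at the follow-ups.
- **Control** (section 2): each participant serves as their own control. Randomisation is only to the baseline length, "8, 12, or 15 evaluation days before the intervention".
- **Effect of surgery** (section 1): the Introduction ranks surgery as the most effective treatment in severe obesity and reports reviews in which depressive symptoms improve in the first months after it and return after the first two years.
- **Relapse.** The Discussion says that the quarterly follow-ups guarantee prevention of relapse, "especially beyond the year and a half or two years". Its later paragraph on implications puts relapse at around two years after surgery.
- **Table 3** marks "Surgical Complications" at pre-treatment only.

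**The concern.** A within-person design attributes change to the intervention when nothing else of consequence changes between the compared time points. Here a second and powerful intervention is scheduled between the 6- and 9-month visits for everyone. Any fall in BMI, or any low BDI-II score, seen from 9 months on has two candidate causes, and the design offers no contrast that tells them apart. If hypothesis 2 is judged at those visits as written, a sustained surgical result could be reported as a maintained effect of the UP. It could also go the other way: a mood problem that follows surgery could be read as the UP wearing off.

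The second issue is the clock. Two years are counted from the end of therapy, while the Introduction and the implications paragraph count relapse from the operation. If surgery comes well after therapy, follow-up ends before the period about which the article makes its claim.

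**Working it through.** **1. Reproduce the plan's split.** Quarterly visits over 24 months: 24 / 3 = 8 visits (3, 6, 9, 12, 15, 18, 21, 24). Two are stated to be before surgery, so 8 − 2 = 6 are after it.

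**2. Check the split against the stated durations.** Inputs from sections 2 and 2.2: a baseline of 8 to 15 days; "The UP will be applied in twelve weekly 2-h online group sessions", which spans 11 to 12 weeks (77 to 84 days) depending on whether the week after the last session is counted; a wait of about 12 months. One month = 365.25 / 12 = 30.44 days. Assumption: the baseline starts at acceptance.

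- End of UP after acceptance: (8 + 77) / 30.44 = 2.79 to (15 + 84) / 30.44 = 3.25 months.
- Surgery after the end of UP: 12 − 3.25 = 8.75 to 12 − 2.79 = 9.21 months.

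This agrees with the plan's placing of the 3- and 6-month visits before surgery. Surgery falls almost on the 9-month visit, so for some participants that visit may come first; the split by visit number is only approximate.

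**3. Time since surgery at the last visit** = 24 − (months from end of UP to surgery).

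| Scenario | Months after surgery at the 24-month visit |
|---|---|
| Wait of 12 months, start at acceptance | 24 − 9.21 = 14.8 to 24 − 8.75 = 15.3 |
| Section 2.2 as stated: surgery between the 6- and 9-month visits | 24 − 9 = 15 to 24 − 6 = 18 |
| Wait of 11 months (assumed) | 15.8 to 16.3 |
| Wait of 13 months (assumed) | 13.8 to 14.3 |
| Wait of 14 months (assumed) | 12.8 to 13.3 |
| Wait of 12 months, start of UP delayed by 3 to 6 months (assumed; 12-day baseline, 12 weeks) | 18.2 to 21.2 |

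In the delayed-start row, surgery comes 12 − 3 − 3.15 = 5.85 to 12 − 6 − 3.15 = 2.85 months after the UP. The 6-month visit is then after surgery, against section 2.2; at a 6-month delay the 3-month visit is too.

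**4. Distance to two years after surgery.** On section 2.2's schedule: 24 − 18 = 6 to 24 − 15 = 9 months short. Reaching two years after surgery would take follow-up to 6 + 24 = 30 to 9 + 24 = 33 months after treatment. No scenario in the table reaches 24 months.

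**5. Is there any contrast that separates the UP from surgery after 6 months?** Everyone receives the UP and everyone has been selected for surgery. The randomised baselines differ by at most 15 − 8 = 7 days, which carries no information about visits 9 to 24 months after therapy. The RCI shows whether an individual changed beyond measurement error, not why. The limitations in the Discussion cover format preference and pilot status; surgery is not mentioned.

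**6. Table 3 against section 2.5.2.** The text defines the surgical-complications measure as a report on how the operation went and on the recovery. That information cannot exist at pre-treatment, where the table places it.

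**The case against.** Several points limit the concern, and most of them stand.

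- **A reader might infer that BMI as a primary outcome is lost to surgery altogether.** The documents do not support that. Hypothesis 1 compares pre-treatment, baseline and post-treatment, all before surgery. Table 3 schedules BMI at each of these and during treatment, weight is checked monthly (section 2.5.2), and the 3- and 6-month visits are also placed before surgery.
- **A reader might infer that one repeated-measures test pools all visits.** Section 2.6 does not say so; it speaks of scores at different times and of post-hoc comparisons. How surgery status enters the analysis is a detail that an article may leave to a fuller document, and its absence is not held against the plan here. No such document, however, could recover a UP effect after surgery from these data.
- **A reader might infer that follow-up misses the whole period from 18 to 24 months.** That is too strong. Section 2.2's range reaches 18 months, a delayed start would put the last visit at about 18 to 21 months, and the Discussion does not say from when its year and a half or two years is counted. What survives is that follow-up falls short of two years after surgery.
- **A reader might want a figure for the surgical effect on BMI.** The document gives none, and the argument needs none.
- **The claims are partly modest.** The implications paragraph speaks of improving the effects of surgery, which is a joint effect; Table 4's list of expected directions omits BMI; and the article asks for caution and later randomised trials. But hypothesis 2 and Table 4's individual results still tie maintenance over two years, on the primary and secondary measures, to the UP.

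**Conclusion.** The point holds in this form. The results from 9 to 24 months, six of eight follow-ups, combine the UP with surgery and cannot support hypothesis 2 as written. This rests on the article's own timetable, on the absence of any comparator without the UP or without surgery, and on its own account of what surgery does to weight and mood. The post-treatment, 3- and 6-month contrasts are free of this problem as long as surgery has not yet taken place for the participant concerned.

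Follow-up ends about 15 to 18 months after surgery on the stated schedule, and at most about 21 months under the assumed delays in starting. Either way it is short of two years after surgery, so the statements that the study guarantees or serves relapse prevention are not supported. The exact figure depends on a wait given only as approximately one year. The Table 3 entry for surgical complications is a separate and minor inconsistency.

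**What to change.** 1. Record each participant's surgery date. Base the BMI endpoint and hypothesis 2 on change from pre-treatment to post-treatment and to those follow-ups that precede that date.
2. Classify later visits by the actual surgery date rather than by visit number, and report them descriptively as UP plus surgery. Do not claim that a surgery term in the model isolates the UP: everyone receives both, and surgery nearly coincides with visit number.
3. State that follow-up ends about 15 to 18 months after surgery, and withdraw or soften the relapse-prevention statements in the Discussion. If two years after surgery is to be observed, follow-up would have to run to about 30 to 33 months after treatment, which is a real extension and not a wording change.
4. Correct Table 3 so that surgical complications are recorded at the post-surgery follow-ups, in line with section 2.5.2.

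Apart from the optional extension, the cost is protocol and analysis wording plus one recorded date, with no extra participants. The price is a narrower long-term claim: maintenance attributable to the UP could be examined only up to surgery, and then still within an uncontrolled pilot.
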